### Study 2: The effect of PUFA levels on executive function is mediated by white matter hyperintensities.

Since the PUFA index is correlated with WMH (figure 3), we performed a mediation analysis to clarify the relationships between PUFAs, WMH, and decline on Trails B. The association between PUFA index and annualized decline in Trails B was re-established in the subset with WMH available (Table 3, model 1). Total WMH also associated with accelerated executive decline (Table 3, model 2). After inserting PUFA index and WMH as simultaneous predictors of Trails B change in the final step, we observed the PUFA index no longer

| Table 3. PUFA and cerebrovascular pathology mediated executive decline |            |                          |      |
|------------------------------------------------------------------------|------------|--------------------------|------|
|                                                                        | Predictor  | Trails B decline (Slope) |      |
|                                                                        |            | $\beta$ (SE)             | P    |
| 1                                                                      | PUFA index | -0.05 (0.02)             | 0.03 |
| 2                                                                      | WMH        | 4.78 (1.39)              | 0.00 |
| 3                                                                      | PUFA index | -0.01 (0.04)             | 0.89 |
|                                                                        | WMH        | 4.86 (2.16)              | 0.02 |
| PUFA index adjusted for baseline PUFAs and WMH for intracranial volume |            |                          |      |

associated with Trails B while WMH remained a significant predictor of accelerated executive decline (Table 3, model 3).

### Study 1 and 2 results suggest that pufas decelerate executive decline in non-demented elders by mechanisms involving less WMH accumulation

#### Study 3: Plasma ICAM-1 predicts rate of decline in cognitive function (Table 4) and rate of increase in WMH (Table 5):

**Study 4: Plasma pufas are inversely associated with plasma soluble ICAM-1 in OBAS cohort.** Figure 4 shows the inverse relationship between plasma pufas and plasma ICAM-1. The cross-sectional linear regression analysis estimate suggests that each 100 ug/mL

Figure 3. Cross sectional association between PUFA index and total WMH volume.

[figure not shown]

Vertical reference line: PUFA index of 110 ug/ml (or 5% of total), horizontal line: 1.25 cm^3 of total WMH. OBAS subjects with MRI were older (mean age=92.4  $\pm$  3.5, range 85–99) compared to those without MRI

Figure 4. PUFAs and ICAM-1

[figure not shown]

| Table 4. Plasma ICAM-1 associated with accelerated cognitive decline in OBAS* |                  |                               |      |                           |        |
|-------------------------------------------------------------------------------|------------------|-------------------------------|------|---------------------------|--------|
|                                                                               |                  | Baseline function (Intercept) |      | Cognitive decline (Slope) |        |
|                                                                               |                  | $\beta$ (SE)                  | P    | $\beta$ (SE)              | P      |
| 1                                                                             | Trails B         | 0.042 (0.087)                 | 0.63 | 0.015 (0.002)             | <0.001 |
| 2                                                                             | Digit Symbol     | -0.014 (0.015)                | 0.33 | -0.003 (0.000)            | <0.001 |
| 3                                                                             | Paragraph recall | 0.004 (0.007)                 | 0.57 | -0.001 (0.000)            | <0.001 |
| 4                                                                             | MMSE             | 0.003 (0.003)                 | 0.38 | -0.001 (0.000)            | <0.001 |
| *Mixed effects models adjusted for baseline plasma ICAM-1                     |                  |                               |      |                           |        |

| Table 5. Plasma ICAM-1 associated with accelerated WMH progression in ADNI**                                                                                     |           |                          |      |                         |       |
|------------------------------------------------------------------------------------------------------------------------------------------------------------------|-----------|--------------------------|------|-------------------------|-------|
|                                                                                                                                                                  | Predictor | Baseline WMH (Intercept) |      | WMH progression (Slope) |       |
|                                                                                                                                                                  |           | $\beta$ (SE)             | P    | $\beta$ (SE)            | P     |
| 1                                                                                                                                                                | ICAM-1    | -0.568 (0.491)           | 0.25 | 0.013 (0.004)           | 0.001 |
| Mixed effects models adjusted for baseline plasma ICAM and total intracranial volume, **Alzheimer's Disease Neuroimaging Initiative, AD subjects excluded, n=404 |           |                          |      |                         |       |

associated with a modest 0.3 ng/mL decrease in plasma ICAM-1 ( $p = 0.02$ , figure 4A). Plasma EPA appears the most significant to plasma ICAM-1 (figure 4B).

increase in plasma PUFA index (EPA+DHA) is

**Study 3 and 4 results suggest that endothelial dysfunction is a risk factor for cognitive decline and white matter disease, and raise the possibility that pufas modulate cerebrovascular function by a mechanism involving ICAM-1**

**Refined hypothetical model for how pufas promote brain health**

[figure not shown]

Page  
8

**Study 4: Pilot randomized trial in Alzheimer's disease confirms the bioavailability and safety of the proposed omega 3 pufa preparation over 1 year.**

This NIA funded (R21AG023805) trial conducted by Drs. [name] and [name] at OHSU tested the bioavailability, safety, and efficacy of pufas and pufas (fish oil extract) + lipoic acid in slowing AD progression. Enrolled subjects were age 55 and older with NINCDS/ADRDA defined AD, a MMSE of 15-26, and CDR  $\leq 1.0$  (Table 5). PUFA supplementation 4 weeks prior to study enrollment or fish intake

**Table 5. Baseline Characteristics**  
(All *P* values for difference between groups > 0.05)

|             | Soybean oil
(n=13)
Mean (SE) | Fish Oil
(n=13)
Mean (SE) |
|-------------|------------------------------------|---------------------------------|
| Age         | 75.2 (10.8)                        | 75.9 (8.1)                      |
| Female      | 54%                                | 39%                             |
| White       | 100%                               | 100%                            |
| College     | 54%                                | 39%                             |
| BMI         | 23.8 (3.1)                         | 26.2 (4.5)                      |
| MMSE        | 22.2 (3.1)                         | 20.7 (2.7)                      |
| RBC DHA (%) | 4.4 (1.0)                          | 5.1 (1.3)                       |
| RBC EPA (%) | 0.55 (0.14)                        | 0.60 (0.23)                     |
| *AD med use | 77%                                | 92%                             |

[figure not shown]

ounces or more/week within a month of study evaluation disqualified patient entry. Thirty-nine subjects were enrolled and

randomized to a placebo (n=13), fish oil only (n=13) or fish oil + lipoic acid (n=13, data not shown). Three fish oil capsules, each

**Figure 6:** Bioavailability of ProOmega 3 Fish Oil (FO) versus placebo: RBC membranes are enriched with EPA and DHA in FO group at 6 months and 12 months (\**p* < 0.05)

**RBC EPA**

**RBC DHA**

23.5 mm long containing a gram of oil concentrate with 325 mg of EPA and 225 mg of DHA each providing a total of 1.65 g of pufas (975 mg EPA and 675 mg DHA) (ProOmega, Nordic Naturals, Watsonville, CA). Three soybean oil capsules of a gram each with same appearance and taste as the active capsules were

administered daily as a control. **Results:** Eighty-seven percent (34/39) of the participants completed the study at 12 months. The bioavailability and safety data for the pufa preparation (fish oil) and placebo are provided in figure 6 and Table 6. Both EPA and DHA levels were higher in the fish oil arm compared to placebo at 6 and 12 months (*p*<0.001) whereas the soybean oil placebo had no such increase in pufa levels at 6 or 12 months compared to baseline. **The fish oil raised the percentage of EPA in RBC's by 2.5% (0.5% to 3.0%) and RBC DHA percentage by 3.5% (4.4% to 7.9%) at 6 and 12 months (figure 6).** Adverse events were monitored monthly. **The fish oil was remarkably well tolerated in this older population (Table 6).** Most AE's were mild and there were no significant differences between groups in number of AE reports or types of AE reported. There were two serious adverse events (death) not related to the study medication, one in the placebo group and one in the pufa group. **Compliance** was monitored by in-clinic pill count every 3 months. Mean compliance range was between 79.4% to 97.8% for all groups at 6 and 12 months and there were no significant differences between

**Table 6. Adverse Events**

|              | Placebo
(n=13) | Fish oil
(n=13) | Fish oil + lipoic
(n=13) | P * |
|--------------|-------------------|--------------------|-----------------------------|------------|
| Cold or Flu  | 3                 | 2                  | 2                           | 0.84       |
| Loose stools | 3                 | 0                  | 3                           | 0.17       |
| Dizziness    | 1                 | 2                  | 2                           | 0.80       |
| Falls        | 2                 | 1                  | 0                           | 0.34       |

\**P*-value reflects a comparison of all groups for each type of AE reported

groups in compliance for fish oil/fish oil placebo or lipoic acid fish oil/lipoic acid fish oil placebo at any time points.

**Summary of the Preliminary Studies Leading to the Primary Hypothesis.** Plasma pufas are inversely associated with WMH volume in non-demented elders; they are also associated with age-related decline in executive function and processing speed and this appears to be mediated by WMH. The pufas explain 28.5% of the total variation in total WMH volume. Blood-based biomarkers of endothelial function (e.g. ICAM-1) are associated with accelerated rate of cognitive decline and WMH progression. PUFAs are inversely associated with plasma ICAM-1, suggesting they may attenuate endothelial dysfunction that we show is significant to brain health. We have experience with the proposed pufa supplement, including its bioavailability and remarkable safety profile in elders. In summary, this body of evidence supports the hypothesis that cerebral small vessel disease and endothelial function are the “locale” for pufa action. These and existing studies justify our emphasis on total WMH, endothelial function and measures of executive function and processing speed skills as the earliest signals of clinical relevance for pufa effects.

**Overall Objective.** The overall objective is to determine if the intervention will prevent late life cognitive decline and dementia, utilizing a reliable and valid biomarker of cerebrovascular disease progression and dementia risk. More concretely, the primary study objective is to determine the effects of pufa supplementation on MRI-derived brain WMH progression in non-demented elders followed for 3 years (Aim 1). Our primary hypothesis is that subjects randomized to pufas will appreciate less total WMH accumulation over the study duration compared to placebo. Another objective is to determine the effects of pufa supplementation on biomarkers of endothelial function over 3 years (Aim 2). The primary hypothesis for Aim 2 is that subjects randomized to pufas will appreciate lower plasma ICAM-1 compared to placebo. We will also explore other biomarkers related to inflammation (VCAM-1, E-selectin, IL-6, TNF-alpha, hsCRP), amyloid (a-beta 40 and 42 amino acid length) and lipid fractions. The third objective is to collect preliminary trial data on the pufa effects on psychometric indices that appear most sensitive to the accumulation of WMH (i.e. executive function).

**Experimental Design.** The design is based upon the observation that WMH volume and advanced age are strong predictors of WMH progression and cognitive decline in non-demented elders. The single-center, randomized, double-blind, placebo controlled clinical trial will test the efficacy of pufas in slowing WMH progression, improving blood-based biomarkers of endothelial function, and slowing decline in executive function and processing speed. The study population consists of non-demented elders age 75 and older who also meet entry criteria for lower plasma pufa status and higher WMH burden at baseline. The intervention is a 50:50 randomization to an active standardized pufa formulation (fish oil extract) vs. a standardized placebo soybean oil over a 3 year period. The pufa formulation and dosage are based on our pilot study and experience with this formulation showing an excellent safety profile and predictable blood concentration. Total WMH volume will be evaluated at entry and annually to analyze the primary outcome. Serially collected plasma samples will be analyzed at baseline, 3 months, 6 months, and then every 6 months to confirm compliance and examine biological activity of the pufas. Neuropsych test emphasis is placed upon domains known to associate with WMH accumulation and pufas and will be collected at baseline and annually. Clinical Dementia Rating-Sum of Boxes and Activities of Daily Living will also be collected in order to determine if there are any more clinically significant effects of the intervention, although we recognize that cognitive and functional change in this relatively healthy population is very modest in this time frame.

### **Study Population**

#### **Inclusion Criteria**

1. Non-demented or mild cognitive impairment, defined as Clinical Dementia Rating =0 or 0.5 and MMSE  $\geq 24$ .
2. Age 75 and older, male and female
3. Total WMH volume  $\geq 5$  cc
4. Plasma PUFA index (EPA + DHA)  $< 110$  ug/ml or  $< 5.5$  weight percent
5. Sufficient English language skills to complete all tests
6. Geriatric Depression Scale –  $15 < 6$  documenting absence of a significant depressive syndrome
7. Sufficient vision and hearing to complete all tests
8. Informant available with frequent (at least 1 hour/day or 1 day/week) contact with subject to verify functional status and CDR rating
9. General health status that will not interfere with the ability to complete the prospective study (these conditions are listed below in the study exclusion list)

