  - g. Anticoagulation therapy: Vitamin K antagonist: warfarin (Coumadin, jantoven), Factor Xa inhibitors: rivaroxaban (xarelto), fondaparinux (arixtra), dabigatran (pradaxa), apixaban (eliquis); Low molecular weight heparins: dalteparin (fragmin), enoxaparin (lovenox)(Incident use of anticoagulant therapy will exclude further study drug allocation. However, subjects will be asked to complete all follow-up visits.)

**Study Supplement and Dose.** Because neuronal functioning is dependent on DHA  and EPA may have vascular effects , we have elected to use a combination supplement. Since these pufas also exist together in nature, this form of supplementation will be less likely to create an unfavorable imbalance in fatty acid metabolism compared to a single constituent form, especially during long-term use in an older population. The form and daily dose of EPA and DHA was chosen because it is a form used in a previous randomized, double-blind, placebo-controlled study in elders with mild to moderate AD (Table 5). This dose was able to significantly increase both EPA and DHA levels in RBC membranes at 6 and 12 months in study participants randomized to receive fish oil (n=13 at both time points), and was associated with an excellent safety profile (Figure and Table 6). This dose also penetrates the threshold plasma levels associated with neuroprotection in our preliminary and published studies. The study supplement will contain one of the following and all study supplements will be taken with meals: 1) Each ProOmega 3 (Nordic Naturals) soft gel contains 1 gram of fish oil concentrate guaranteed to have a concentration of long-chain omega 3 fatty acid ethyl esters at 70%, primarily EPA (325 mg/g) and DHA (225 mg/g). Three capsules is the daily dose, which will provide a total of 1650 mg of omega 3 pufas (975 mg EPA + 675 mg DHA) per day; 2) Placebo oil contains soybean oil.

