**Screen I (visit 1).** Informed consent will be obtained from both the study subject and the study partner when they arrive at the clinic. Demographics and general medical history will be obtained including psychiatric history, family history and history of allergies. A general physical and neurological exam will be performed including vital measures. To accommodate participants' schedules, the general physical and neurological exam may be performed at Screen II (visit 2) instead. A review of pre-study medications for up to 30 days prior to screening will occur. A non-dementia status will be confirmed using the same diagnostic protocol used in the Oregon Alzheimer's Disease center. The MMSE, CDR, GDS, screening labs, safety labs, and the addition of a plasma PUFA index (EPA + DHA in ug/mL or % <5.5% total fatty acids) will be performed. This information will be used to establish the eligibility as outlined under protocol Inclusion/Exclusion criteria. Screen I/Visit 1 will take approximately 2 hours. **If visits 1 and 2 are combined, the participant will be asked**

**to come in fasted for their appointment, and study staff will wait to randomize the participant pending meeting all inclusion criteria.**

Screen I Fail Procedure: Participants who are ineligible for study will be notified and provided an explanation for their ineligibility. The total number of screen failures and justification will be documented. Plasma PUFA index failures are counted and documented.

**Screen II (visit 2).** MRI will identify subjects with high WMH. MRI screen is performed within 56 days of the Screen I (visit 1). This brain scan determines WMH eligibility as outlined in the protocol Inclusion / Exclusion criteria. This visit will take approximately 3 hours. Participant will also complete a Food Frequency Questionnaire administered by a nutritionist in clinic to answer questions and assure complete data, and central blood pressure will be measured by a research coordinator. The general physical and neurological exam will also be completed if not done at Screen I (visit I).

Screen II Fail Procedure: Participants who are ineligible for study will be notified and provided an explanation for their ineligibility. The total number of screen failures and justification will be documented. WMH volume failures are counted and documented.

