**Adverse events.** Adverse events will be monitored in “real time” with weekly review of AE’s with study staff using clinical judgment to determine reporting to IRB and FDA. An external data safety monitoring board (DSMB) will convene biannually to study unblinded data on AE coded by organ system. Although assessment of AEs will also include solicitation of non-specific change (e.g., “do you feel different since beginning the treatment?”), a 12-item AE checklist covering all major organ systems will be included to probe for AEs. The nature of each AE, its severity (mild, moderate, or severe), its likely relationship to study treatment (definite, probable, possible, not related, or unknown), its duration, and any necessary treatment modifications or adjustments will be recorded. In addition to the monitoring and recording of AEs at each 3 month subject contact, labs to assess basic metabolic function (including liver function tests), CBC and PT/INR are performed at screening and at months 6, 12, 18, 24 and 36. Incident use of oral anticoagulant therapy is identified through subject interview that occurs every 3 months. Incident anticoagulation therapy cases are asked to stop the supplement and complete complete the remaining follow up visits. Participants will be reminded and encouraged during clinic visits and phone checks to contact the study coordinator or investigator if a moderate or serious AE occurs.

**Compliance:** Compliance will be measured in-clinic by pill count. In addition to the in-clinic checks on compliance, each subject will receive a phone call to check on compliance every 3 months. If a subject’s compliance drops < 80% at any time, they will be contacted by the trial coordinator by phone to find out why

and to aid the subject in finding ways to increase compliance. Although plasma fatty acid measurement is an independent measure of compliance, knowing the results of fatty acids levels during the study would un-blind the study. Plasma PUFA index will be used during data analysis to corroborate pill count.

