**Informed Consent:** Prior to the in-clinic screening visit, all potential participants and their study partners will be mailed a copy of the IRB approved consent/HIPAA authorization form so that they may be fully informed of all aspects of their participation in the study. At the time of consent one of the study investigators, coordinators, or the research assistants will review the consent/HIPAA authorization form and then will ask the participant and study partner to describe key points in the consent form (e.g. purpose of study, knowledge of placebo control group, length of study) before the consent form will be signed. Once the participant signs the consent form he or she will continue with screening assessments.

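### No entry criterion excludes known allergy to fish, soy or a capsule ingredient, although both blinded arms take fish oil or soybean oil capsules (minor participant-safety point)

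*Protocol*

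**What the plan says.** **Products.** The protocol, under Experimental Design, describes a "50:50 randomization to an active standardized pufa formulation (fish oil extract) vs. a standardized placebo soybean oil over a 3 year period". Study Supplement and Dose specifies three one-gram fish oil soft gels a day for the active arm and says of the comparator: "Placebo oil contains soybean oil". Under Blinding and Randomization, neither participants nor study staff know the assignment.

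**Allergy history.** At Screen I, "Demographics and general medical history will be obtained including psychiatric history, family history and history of allergies". After listing the cognitive and mood scales, laboratory tests and plasma fatty acid index, the same paragraph adds: "This information will be used to establish the eligibility as outlined under protocol Inclusion/Exclusion criteria".

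**Entry criteria.** Inclusion criterion 9 is the only general-health criterion. It requires health that will not interfere with the "ability to complete the prospective study (these conditions are listed below in the study exclusion list").

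**Product risks.** Section 1.C (Potential Risks) names belching, gastrointestinal effects and a bleeding concern for fish oil, and mild gastrointestinal effects for soybean oil. It calls the risks of both minimal and does not discuss allergy.

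**The concern.** The two study products come from fish and from soy, and assignment is blinded. Staff who know of a participant's fish or soy allergy therefore cannot steer that person to the other arm. The usual protection is an entry criterion on known allergy to the products. Here the information is collected, but no criterion acts on it.

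What is at stake is who may be dosed. A three-month supply is dispensed at baseline, and the next scheduled contact is at month 3, so whatever protects a person with a known allergy should operate before the first capsule. The statistical design is not involved: the sample size, the primary comparison and the analysis model are unaffected.

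**Working it through.** No figure in the protocol needs reproducing. The check is a full reading of the criteria against the screening and safety text.

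**1. Where allergy appears.** In the protocol text available, it appears once, in the Screen I medical history. It does not appear in the entry criteria, in the risk section or in the data and safety monitoring plan.

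**2. Criteria naming allergy, hypersensitivity or intolerance.**

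| List | Items | Naming allergy |
|---|---|---|
| Inclusion criteria | 9 | 0 |
| Exclusion criteria | 14 | 0 |
| Medication sub-items 14a to 14g | 7 | 0 |

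**3. Could another criterion cover it indirectly?**
- Inclusion 9 is general, but its parenthesis sends the reader to the exclusion list for the conditions meant, and allergy is not on that list.
- Exclusion 12 (illness needing more than one clinician visit a month) would not normally catch a food allergy managed by avoidance.
- Exclusion 14c concerns stable dosing of over-the-counter supplements. Exclusion 14d concerns prior omega-3 use and washout. Neither deals with tolerance of the product.
- No criterion lets the investigator exclude someone at discretion.

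**4. What follows.** A person who meets every listed criterion and has a known fish, soy or capsule-ingredient allergy is eligible as written.

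**5. How the protocol treats another product-specific caution.** Exclusion 14g bars anticoagulant users at entry, and during follow-up "Incident anticoagulation therapy cases are asked to stop the supplement". This shows only that the exclusion list is where the protocol puts such cautions. It is not evidence about allergy.

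**6. Size.** The protocol gives no prevalence of such allergy and no probability of a reaction. For scale only, assume that a share *p* of otherwise eligible people have such a known allergy:
- number admitted among 150 = 150 × *p*
- *p* = 0.1%: 150 × 0.001 = 0.15
- *p* = 2%: 150 × 0.02 = 3

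The range for *p* is an assumption with no source in the protocol. The result counts people admitted, not people harmed. How many would react cannot be estimated.

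**The case against.** The strongest reply is that no harm is shown. The active product is a concentrate of fatty acid ethyl esters, and the protocol gives neither the residual protein in either oil nor the shell ingredients. Section 1.C rates the risks as minimal and cites regulatory recognition of the dose as safe. The 39-person pilot reported mostly mild events, and its table lists no allergic reaction. This stands: a reader might infer that the trial exposes people to an established allergic hazard, and the protocol does not support that. The pilot is weak reassurance, however. It is small and does not say whether anyone with a known allergy took part.

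A second reply is that eligible does not mean obliged to enrol, and that safeguards exist. Staff may decline to enrol someone, and a person may decline a product they know they cannot take. At consent, staff "will review the consent/HIPAA authorization form and then will ask the participant and study partner to describe key points in the consent form"; the form itself is not in the copy reviewed and may carry a warning. Staff review adverse events weekly as they arise, with contacts every three months and "a 12-item AE checklist covering all major organ systems will be included to probe for AEs". Participants are urged to report moderate or serious events and are given a telephone number for severe side effects. All this stands and lowers the risk. However, most of it operates after dosing has begun, and none of it is an entry rule. The protocol also does not say who reviews the allergy history.

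A third reply is that recording allergies is routine. Family history sits in the same list and feeds no criterion either. The sentence tying Screen I information to eligibility follows the scales and laboratory tests and may refer only to those. This also stands. A reader might infer that the Screen I text contradicts the criteria, but the wording is too loose for that. The point is a gap in the criteria and does not depend on how that sentence is read.

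Finally, a reader might infer that the low plasma EPA+DHA criterion draws in people who avoid fish because of allergy. The protocol offers no data on this, and nothing here relies on it.

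**Conclusion.** The point holds as a minor participant-safety improvement, worth considering. The textual part is firm: the criteria contain no allergy exclusion, and inclusion 9 does not supply one, so a person with a known allergy to fish, soy or a capsule ingredient meets the written criteria for the blinded capsules.

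The clinical consequence is not established. That such a person could react is an assumption, and the number who would be admitted is unknown. The point also assumes that no allergy rule stands in material outside the copy reviewed; a warning in the consent form would help but would not be an entry criterion. There is no effect on power or analysis.

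**What to change.** Add one exclusion criterion: known allergy or hypersensitivity to fish or fish oil, soy, or any ingredient of either capsule. Apply it to the allergy history already taken at Screen I, before randomisation. A sentence on allergic reaction in section 1.C would be a sensible but optional companion.

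The change needs one line and no new data collection. Its cost is a few extra screen failures, in a number that cannot be stated without a prevalence. Under the assumed range above, the extra otherwise eligible candidates needed to still randomise 150 run from 150/0.999 − 150 = 0.15 to 150/0.98 − 150 = 3.06. The protocol estimates 5,256 potential participants. That figure comes from a database scan of people aged 80 and older, whereas entry is from age 75, so it only roughly indicates that the loss can be absorbed.
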